## Abstract

**Background:**

Secondary peritonitis is a severe condition with a 20–32% reported mortality. The accepted treatment modalities are vacuum-assisted closure (VAC) or primary closure with relaparotomy on-demand (ROD). However, no randomised controlled trial has been completed to compare the two methods potential benefits and disadvantages.

**Methods:**

This study will be a randomised controlled multicentre trial, including patients aged 18 years or older with purulent or faecal peritonitis confined to at least two of the four abdominal quadrants originating from the small intestine, colon, or rectum. Randomisation will be web-based to either primary closure with ROD or VAC in blocks of 2, 4, and 6. The primary endpoint is peritonitis-related complications within 30 or 90 days and one year after index operation. Secondary outcomes are comprehensive complication index (CCI) and mortality after 30 or 90 days and one year; quality of life assessment by (SF-36) after three and 12 months, the development of incisional hernia after 12 months assessed by clinical examination and CT-scanning and healthcare resource utilisation. With an estimated superiority of 15% in the primary outcome for VAC, 340 patients must be included. Hospitals in Denmark and Europe will be invited to participate.

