## Background

Perforation of the gastrointestinal tract is the most common cause of secondary peritonitis [1, 2]. The underlying conditions may be appendicitis, anastomotic dehiscence, perforated diverticulitis, intestinal ischemia, or gastroduodenal ulcer, being the most common [3–7]. Faecal peritonitis is associated with high mortality and morbidity rate, with a reported 28-days mortality up to 20%, increasing to 32% at six-month follow-up [8]. Age, comorbidity, time to intervention, and the extent of peritonitis are important risk factors [7, 9–14]. A prerequisite for non-failure is sufficient source control, antibiotics, and in cases with organ dysfunction, postoperative intensive care treatment may be necessary [15–19]. Despite sufficient treatment, the risk of postoperative abdominal complications is high, and several patients may undergo a reoperation (s) to reveal and treat the complications. Another risk is the development of abdominal compartment syndrome. To manage this, three different strategies may be employed: a planned relaparotomy (PR), a relaparotomy on-demand (ROD), or the open abdomen (OA) principle [2, 5, 20–23]. A randomised controlled trial on PR versus ROD in patients with secondary peritonitis due to gastrointestinal perforation, including 232 patients, showed no significant difference in 1-year mortality (36% vs. 29%) and morbidity (44% vs. 40%) [20]. ROD resulted in significantly fewer relaparotomies and lower hospital-related healthcare costs.

A guideline [19] and consensus report [24] from the World Society of Emergency Surgery recommend ROD or VAC as the preferred treatment strategies for intra-abdominal infections with peritonitis and non-traumatic abdominal emergencies. The benefit of primary abdominal closure and ROD strategy is that patients do not require further scheduled operations. The risk is a delay in treatment for ongoing abdominal sepsis, other serious complications, and abdominal compartment syndrome, which may be difficult to recognise clinically in the severely ill patient [25–28]. Delays in treating severe complications might increase the risk of morbidity and mortality [9, 11, 14]. The advantages of VAC are a planned inspection of the abdominal cavity and the possibility to diagnose and treat potential or overt abnormalities on time. The risk is the development of enteroatmospheric fistula, difficulties in abdominal wound closure, and the development of an incisional hernia [29, 30].

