Although the validated CCI may be the best parameter to monitor postoperative complications and morbidity, there are no reliable data in the literature on CCI from this specific group of patients. Therefore, we could not make a meaningful sample size calculation based on CCI alone. Peritonitis-related complications described in the RCT by Van Ruler et al. were the best estimate for the postoperative complications and morbidity we could find in the literature and were used for the study's sample size calculation [20].

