#### Sample size and power

With an expected peritonitis-related complications rate of 40% in the ROD group [20] and 25% in the VAC group [42, 44], the desired power of 80%, a significance level of 0.05, and an expected drop-out of 5%, a total of 340 patients should be included.

As the CCI distribution in this group of patients is unknown, we could not perform an explicit sample size calculation for this secondary outcome. A 0.32 standard deviation difference in mean CCI between the two groups could be detected with 80% power with this sample size.

To ensure sufficient recruitment, the study will be multicentre and European. Eight active centres have been included, and two are in process. Randomisation tools along with eligibility criteria are accessible through our website. The workflow and relevant contact details appear on posters at the participating departments. Study progress will be available on the website.

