The interim analysis will be performed at 25%, 50%, and 75% of recruited patients on the primary outcome after 30-days to detect significant differences between groups at the earliest possible time, ultimately leading to the termination of the study. We have adjusted our power calculation to the interim analyses using the O'Brien–Fleming method. The study group will have access to the results of the interim analyses and may make the final decision to terminate the study.

All of the above analyses will be performed as both intention-to-treat (patients will be analysed according to their randomisation group) and per-protocol analysis (what actually happened). The main analyses will be performed as complete case analyses. Multiple imputations will impute missing values in a supplementary analysis, including baseline characteristics as predictors.

*P* values < 0.05 will be considered statistically significant. Statistical calculations will be performed using Stata software (version 15, Stata Corp LP, Texas, USA).

In the VACOR-Microdialysis sub-study, the parameters will be compared using descriptive statistics for continuous and discrete variables. Repeated measurement across time points will be compared by mixed-effects regression models, including the interaction between time points and operation method and a random intercept for each patient. In addition, normality assumptions will be graphically assessed using quantile–quantile plots.

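### The primary outcome has three unranked time points, the stopping looks use one of them, and the planning rates are tied to none, so the confirmatory test and its power are not fixed

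*Protocol article*

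**What the plan says.** All references are to the protocol article.

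- **Endpoint.** Abstract, Methods: "The primary endpoint is peritonitis-related complications within 30 or 90 days and one year after index operation". The Objectives section lists the same three horizons under the primary objective. Neither place ranks them.
- **Test.** Statistical analysis describes a chi-square comparison of the primary outcome, reported as a relative risk, and names no time point. Later in the section a general significance threshold of P < 0.05 is given.
- **Interim looks.** These take place at a quarter, half and three quarters of recruitment, "on the primary outcome after 30-days to detect significant differences between groups at the earliest possible time", and may lead to termination. O'Brien–Fleming is mentioned as an adjustment of the power calculation for these looks. The study group sees the interim results and may decide to stop.
- **Planning rates.** Sample size and power: "With an expected peritonitis-related complications rate of 40% in the ROD group" and "25% in the VAC group [42, 44". No horizon is attached to either figure.
- **Source of the 40%.** The text after Table 2 says that the complications reported in the earlier randomised trial of planned versus on-demand relaparotomy "were used for the study's sample size calculation [20". The Background reports that this trial "showed no significant difference in 1-year mortality (36% vs. 29%) and morbidity (44% vs. 40%) [20".

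**The concern.** A trial needs one primary comparison, or a stated rule for combining several. Here three cumulative versions of the same outcome share primary status, and the parts of the design that depend on the endpoint do not clearly refer to the same version. The looks use 30 days, the control rate appears to be a one-year rate, and the final test has no time point.

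Two things are at stake. First, error control: nothing in the text prevents a claim of success at whichever horizon turns out favourably, and O'Brien–Fleming deals with repeated looks, not with several horizons. Secondly, power: 80% is a statement about one pair of rates, and the reader cannot tell which of the three tests it describes. Because the study group has access to interim results, the choice of horizon should be settled before any comparative data are seen.

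**Working it through.** **1. Reproducing 340.** Inputs from Sample size and power: 40% versus 25%, 80% power, significance level 0.05 (two-sided assumed), 5% drop-out. Equal allocation is assumed.

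n per arm = [1.960·√(2·0.325·0.675) + 0.842·√(0.40·0.60 + 0.25·0.75)]² / 0.15² = (1.298 + 0.550)² / 0.0225 ≈ 152.

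- Without continuity correction: 304 in total; 304/0.95 = 320; with a four-look O'Brien–Fleming factor of 1.024, 328.
- With continuity correction: 165 per arm, 330 in total; 330/0.95 ≈ 348.

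The stated 340 is within 3% of the last figure. It is sound for one 40% versus 25% comparison.

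**2. Power for that one comparison.** 340 × 0.95 = 323 evaluable, 161.5 per arm.

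Power = Φ[(0.15·√161.5 − 1.298)/0.654] = Φ(0.93) = 82% (fixed design).

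**3. Power at other horizons.** The article gives no 30- or 90-day rates, so these ROD rates are assumptions. Two ways of carrying the effect over are shown: constant relative risk (25/40 = 0.625) and constant 15-point difference.

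| ROD rate | Power, RR 0.625 | Power, 15 points |
|---|---|---|
| 40% | 82% | 82% |
| 35% | 75% | 86% |
| 30% | 65% | 90% |
| 25% | 55% | 95% |

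The direction depends on which assumption is made. The conclusion is that power at the other horizons is not shown, not that it is low.

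**4. Error rate under no difference.** For nested cumulative outcomes with rates a < b, the correlation of the test statistics is √[a(1−b)/(b(1−a))]; for 20% and 40% this is √(0.12/0.32) = 0.61. The table gives simulated probabilities of at least one nominal success. The one-year rate is set at 40% and the earlier rates are assumed. The O'Brien–Fleming boundary for four looks uses C = 2.024, applied to the 30-day outcome at the three interims.

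| Rates at 30 d / 90 d / 1 y | Any of three at 0.05 | 30-day looks + three tests at 0.05 |
|---|---|---|
| 35/38/40% | 7.7% | 8.2% |
| 30/35/40% | 8.9% | 9.3% |
| 20/30/40% | 10.4% | 11.0% |
| 15/25/40% | 11.2% | 11.7% |

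Normal-approximation and patient-level simulations agree to within a few tenths of a point. Three independent tests would give 1 − 0.95³ = 14.3%, but nesting rules that figure out. Using the O'Brien–Fleming final level (0.043) for all three tests, with rates from 35/38/40 to 20/30/40, still gives 7.3–9.7%. With 30-day looks and only a one-year test at 0.05, the figure is about 6–6.5%.

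**5. The alternative of keeping all three as primary.** Bonferroni at 0.05/3 = 0.0167 needs 203 per arm, 406 in total, or 406/0.95 ≈ 428 with drop-out. With 323 evaluable, power per time point would be 69%.

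**The case against.** The strongest reply is that the article describes a single comparison of the primary outcome and only a general threshold. No sentence says that three tests will be run, and a hierarchy or alpha allocation is commonly left to the analysis plan. That is right as far as it goes. A reader might infer that three tests at 0.05 are planned; the documents support only that this is not excluded. What stands is that the article itself gives the primary outcome three horizons, in two places, and an analysis plan naming one would have to narrow that definition.

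A reader might also take 40% versus 25% to be a one-year contrast. In the Background, the one-year label is attached to mortality and carries over to morbidity only on the natural reading. The 25% comes from other sources and has no horizon.

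It is tempting to argue that a 30-day stop would miss the late harms of VAC, namely hernia and fistula. The documents do not carry this. Table 1 counts hernia only with obstruction, or when disabling and needing surgery, and hernia overall is a separate 12-month secondary outcome. Nothing makes fistula a late event. Many Table 1 items could plausibly be early, which would bring the horizons closer together and reduce the error inflation.

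Finally, monitoring on an early outcome is a legitimate choice, and the looks themselves add only about half a percentage point to the three-test figure.

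**Conclusion.** The point holds in this form: three unranked primary time points, a general 0.05 threshold, stopping looks on the 30-day version, and one planning contrast without a horizon. Followed as written, the chance of a false claim at one or more horizons is about 8–11%, or 8–12% with the looks, against a nominal 5%. These figures assume two-sided tests, a one-year rate of 40%, and 30-day rates between 15% and 35%; they are smaller the more events occur early. Choosing one year alone while keeping unaccounted 30-day looks would leave about 6–6.5%.

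The figure of 340 is not wrong, and the documents do not show that the trial is underpowered at 30 or 90 days. They show 82% power for one 40% versus 25% comparison and leave open which time point that is.

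**What to change.** 1. Name one primary time point. One year is the natural candidate if the sponsor confirms that 40% versus 25% is a one-year contrast; 340 then stands. If another time point is chosen, state its rates and redo the sample size.
2. State the horizon of both planning rates.
3. Make the other two time points secondary, tested in a fixed order and only after a significant primary result.
4. State that the 30-day looks are a stringent early check that does not itself constitute the primary result, and account for them in the final significance level, allowing for the fact that they use a different version of the outcome. Alternatively, align them with the primary time point.

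The cost of items 1–3 is wording in the protocol and analysis plan and a registry update. No extra data are needed, because Data collection and participant timeline already schedules record reviews at one month, three months and one year. Item 4 costs a short calculation of the final level. Moving the looks to one year instead would delay each by about eleven months; this is a trade-off for the sponsor and not a requirement. The downside is that a difference at an early horizon alone could no longer be claimed as the primary result.

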**Discussion:**

There is no robust evidence for choosing either open abdomen with VAC treatment or primary closure with relaparotomy on-demand in patients with secondary peritonitis. The present study has the potential to answer this important clinical question.

***Trial Registration*:**

The study protocol has been registered at clinicaltrials.gov (NCT03932461). Protocol version 1.0, 9 January 2022.

**Supplementary Information:**

The online version contains supplementary material available at 10.1186/s13017-022-00427-x.

## Background

Perforation of the gastrointestinal tract is the most common cause of secondary peritonitis [1, 2]. The underlying conditions may be appendicitis, anastomotic dehiscence, perforated diverticulitis, intestinal ischemia, or gastroduodenal ulcer, being the most common [3–7]. Faecal peritonitis is associated with high mortality and morbidity rate, with a reported 28-days mortality up to 20%, increasing to 32% at six-month follow-up [8]. Age, comorbidity, time to intervention, and the extent of peritonitis are important risk factors [7, 9–14]. A prerequisite for non-failure is sufficient source control, antibiotics, and in cases with organ dysfunction, postoperative intensive care treatment may be necessary [15–19]. Despite sufficient treatment, the risk of postoperative abdominal complications is high, and several patients may undergo a reoperation (s) to reveal and treat the complications. Another risk is the development of abdominal compartment syndrome. To manage this, three different strategies may be employed: a planned relaparotomy (PR), a relaparotomy on-demand (ROD), or the open abdomen (OA) principle [2, 5, 20–23]. A randomised controlled trial on PR versus ROD in patients with secondary peritonitis due to gastrointestinal perforation, including 232 patients, showed no significant difference in 1-year mortality (36% vs. 29%) and morbidity (44% vs. 40%) [20]. ROD resulted in significantly fewer relaparotomies and lower hospital-related healthcare costs.

A guideline [19] and consensus report [24] from the World Society of Emergency Surgery recommend ROD or VAC as the preferred treatment strategies for intra-abdominal infections with peritonitis and non-traumatic abdominal emergencies. The benefit of primary abdominal closure and ROD strategy is that patients do not require further scheduled operations. The risk is a delay in treatment for ongoing abdominal sepsis, other serious complications, and abdominal compartment syndrome, which may be difficult to recognise clinically in the severely ill patient [25–28]. Delays in treating severe complications might increase the risk of morbidity and mortality [9, 11, 14]. The advantages of VAC are a planned inspection of the abdominal cavity and the possibility to diagnose and treat potential or overt abnormalities on time. The risk is the development of enteroatmospheric fistula, difficulties in abdominal wound closure, and the development of an incisional hernia [29, 30].

The method with VAC was initially introduced in damage control trauma surgery and has gained increasing use in the treatment of complicated intra-abdominal infections [21, 31–43]. A systematic review and meta-analysis by Atema et al. in 2015 showed an incidence of 14.6% for enteroatmospheric fistula (EAF) and 48.5% for incisional hernias in the group treated with VAC, where 82% of the population was treated for peritonitis. The mortality varied between 21.5 and 30.0%. The VAC procedure can be applied and modified in several ways. The most common are fascial traction methods (mesh mediated or non-mesh mediated), the applied vacuum pressure and the interval for changes of the VAC [42]. The VAC treatment in the present study will be performed with a non-mesh-mediated fascial traction method and narrowing technique. A retrospective study from our institute using this technique, including 115 patients with secondary peritonitis, found a mortality rate of 17% and EAF of 3.5%; secondary closure was obtained in 92% of the patients [44].

The present study will aim to compare the postoperative results of ROD and VAC in patients with secondary peritonitis by a randomised controlled trial with peritonitis-related complications as the primary outcome; comprehensive complication index (CCI), mortality, quality of life, the development of incisional hernia, and hospital care utility and costs were the secondary outcomes.

## Objectives

PrimaryPeritonitis-related complications (Table 1) within 30 or 90 days and one year after index surgerySecondaryCCI within 30 or 90 days and one year after index surgeryMortality within 30 or 90 days and after one yearSOFA score and C-reactive protein (CRP) measured in the first seven days after index laparotomyIncisional hernia rate after 12 months assessed by clinical examination and abdominal CT-scanQuality of life after 3 and 12 months assessed by the SF-36 questionnaireHospital care utility within three months after index surgery (Table 2)TertiaryThe concentration of lactate, glycerol, pyruvate, glucose, and cytokines in the peritoneal fluid in a subgroup of 10 patients from each group measured by intraperitoneal microdialysis on postoperative days 0–4

**Table 1 Tab1:** Peritonitis-related complications

Disease-related major morbidity needing readmission and conservative treatment but not surgery
Fistula: non-anatomical connection between intestine and cutis, communication between GI tract and external atmosphere or between 2 hollow organs
Wound dehiscence/incisional hernia with obstruction: full-thickness discontinuity in the abdominal wall with bulging of abdominal content
Abscess needing percutaneous drainage: pus-containing non-pre-existing cavity confirmed by positive Gram stain or culture
Renal failure: urine production < 500 mL/24 h with rising levels of blood urea nitrogen and creatinine combined with dehydration (decreased circulating volume with elevated haematocrit needing intravenous rehydration) based on inadequate oral intake, nausea/vomiting, or both (only when needing readmission)
Myocardial infarction (electrocardiogram and enzyme changes suggestive of myocardial infarction or needing admission to coronary care unit), pulmonary embolus (ventilation-perfusion mismatch on lung scintigraphy), or cerebrovascular accident (ischemic or non-ischemic with persistent paresis or paralysis without previous history)
Gastric or duodenal bleeding: needing endoscopic treatment or embolisation therapy
Respiratory failure due to pneumonia, pleural effusion, or pulmonary oedema and needing oxygen therapy or mechanical ventilation
Urosepsis: urinary tract infection with positive urine and blood cultures and circulatory shock

Disease-related major morbidity needing surgical intervention during first admission or readmission
Incisional hernia: full-thickness discontinuity in abdominal wall with bulging of abdominal contents with or without obstruction with disabling concerns interfering with daily activities
Bowel obstruction or herniation due to intra-abdominal adhesions: diagnosis must be confirmed during surgery
Burst abdomen: complete midline or transverse discontinuity in abdominal wall
Abdominal compartment syndrome: intra-abdominal hypertension ≥ 25 mm Hg with tense abdomen and with increasing respiratory failure, renal failure, or both, measured by the urinary bladder pressure method (modified Burch criteria)
Fistula: non-anatomical connection between intestine and cutis, communication between GI tract and external atmosphere or between 2 hollow organs
Intra-abdominal bleeding: only when septic bleeding after index laparotomy or relaparotomy or surgical bleeding after relaparotomy but not after index laparotomy
Intra-abdominal haematoma needing surgical evacuation
Perforation of visceral organ confirmed at surgery
Anastomotic leakage: anastomotic leak on contrast imaging needing surgery or contrast-enhanced computed tomography scan, confirmed at relaparotomy
Ischemia or necrosis of a visceral organ: critically reduced blood flow to an intra-abdominal organ causing tissue loss, confirmed at pathological examination
Enterostomy dysfunction due to prolapse, stenosis, or retraction
Gastric or duodenal ulcer bleeding needing intervention of any type

Reference Table 1: van Ruler O, Mahler CW, Boer KR, Reuland EA, Gooszen HG, Opmeer BC, de Graaf PW, Lamme B, Gerhards MF, Steller EP, van Till JW, de Borgie CJ, Gouma DJ, Reitsma JB, Boermeester MA; Dutch Peritonitis Study Group. Comparison of on-demand vs planned relaparotomy strategy in patients with severe peritonitis: A randomised trial. JAMA. 2007 Aug 22;298(8):865–72. Available from: http://dx.doi.org/10.1001/jama.298.8.865

**Table 2 Tab2:** Health care utility

Length of admission at ICU (Total number of days in a three-month period)
Length of admission at ward (Total number of days in a three-month period)
VAC—Time from index operation to primary closure
Total amount of VAC dressing changes (number of times)
Number of scheduled VAC changes
Number of re-operations with VAC
Number of re-operations
Number of radiologic interventions during admission(s)
Number of computed tomography scans after index operation
Number of days alive outside the ICU in a three-month period

Although the validated CCI may be the best parameter to monitor postoperative complications and morbidity, there are no reliable data in the literature on CCI from this specific group of patients. Therefore, we could not make a meaningful sample size calculation based on CCI alone. Peritonitis-related complications described in the RCT by Van Ruler et al. were the best estimate for the postoperative complications and morbidity we could find in the literature and were used for the study's sample size calculation [20].

